### Group assignment

Clustered treatment assignment will be performed. First, two urban municipalities of the Metropolitan Region of Santiago, Chile, which collaborate with the Faculty of Medicine of Universidad de Chile and have at least two primary health care clinics, will be randomly selected through simple random sampling. Municipalities with a high Human Development Index, a high percentage of immigrants and older population, and psychiatry residents working in primary health care clinics will be excluded. In each selected municipality, the two primary health care clinics with the highest registered number of patients will be randomly assigned to the active or the control arm, through simple random sampling, thus selecting a total of four primary health care centers, one from the intervention arm and one from the control arm, in each selected municipality. This matching was done in order to ensure similarity between the patients’ socioeconomic levels and the administration and organization of the primary care centers, since all centers within a municipality are overseen by the same administration.

### Data collection

All participants will be assessed at baseline and at 3 and 6 months after recruitment. Independent interviewers blind to treatment assignment evaluated participants at 3 and 6 months after baseline assessment. The interviewers received an 8-h training to ensure standardization of data collection, which will be performed using digital PDF forms. Interviewers and patients will use computer tablets for data entry.

### Data management

Data collection is expected to be completed in late 2015. After each evaluation is complete, encrypted data entry forms will be sent by the interviewers via secure password-protected e-mail to the data management center. No copy of the data will remain on the computer tablets. Information will be compiled and exported to the CSV format for analysis in the SPSS software [37]. Only the principal investigator and co-investigator in charge of data management and analysis will have access to these data. Data will be encrypted and stored in a local hard drive. Subjects' identifying information will be eliminated from the database and preserved in a secure location. Data will only be identified by a unique ID code to ensure participants' anonymity.

### Data analysis

Data analysis will be performed using SPSS software [37], with which scores of the used scales will be calculated. Data and presentation of the results will be in accordance with CONSORT guideline for randomized clinical trials [38] as well as its extensions to cluster and non-pharmacological interventions, with the primary comparative analysis being conducted on an intention-to-treat basis. Initially, we will conduct descriptive analysis to assess the balance between the two groups. The primary analysis will employ multivariable linear regression to investigate differences in mean symptom scores (the primary outcome measure) between groups at 3 and 6 months after randomization, adjusting for baseline outcome variables if imbalances are identified. Sensitivity analysis based on different assumptions will be conducted to investigate the potential effects of missing data. Similar analysis will be carried out for secondary outcome measures.

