### Sample size

Sample size calculation was done based on two studies previously carried out in Chile [36, 15]. A randomized clinical trial that compared pharmacotherapy monitored by telephone with usual care in primary care clinics in Chile found a recovery rate for depressive disorders of 62 % in the intervention group versus 38 % in the control group [36], having an effect size of 20 %. Since the current study protocol aims to test whether the intervention is better than usual care, a one-sided test is appropriate to detect an effect. Moreover, it is expected that the intervention will have a favorable effect ruling out the possibility of a statistically significant negative effect. To detect a difference of 20 %, in a one-sided model, with an alpha of 5 % and power of 80 %, 152 depressed persons, 76 in each group (intervention and control), will be required for the study. Using a database from another study comprising 201 persons treated for depression in seven primary care clinics [15], an intraclass correlation coefficient (ICC) of 0.03839 was estimated. Therefore, a design effect of 2.42 was determined, based on the previously calculated ICC and the use of four clusters (primary care clinics). After applying the design effect, the sample needed increased to 368 depressed persons. Considering a retention rate of approximately 85 %, 434 depressed cases will be required for the study, hence 109 cases in each of the four primary health care clinics.

Finally, a group of four primary health care clinics was chosen for two reasons: the usual flow of patients with depression presenting at each of the participating primary care clinics, which allows for a high number of potential participants per clinic, and financial constraints restricted the number of clusters, since having more primary care clinics would put in jeopardy the feasibility of the study.

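### The named primary analysis is a patient-level linear regression with no allowance for clinic, although four clinics are randomised and the sample size assumes an ICC; run as written, its standard errors are too small.

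*Protocol article*

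**What the plan says.** Three sections of the protocol article bear on this.

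- **Group assignment.** Clinics are the unit of randomisation, paired by municipality: "the two primary health care clinics with the highest registered number of patients will be randomly assigned to the active or the control arm". Two municipalities give four clinics, one per arm in each.
- **Sample size.** From an earlier database of 201 persons in seven clinics, "an intraclass correlation coefficient (ICC) of 0.03839 was estimated". A design effect of 2.42 takes the requirement from 152 to 368, and an 85 % retention rate takes it to 434, or 109 per clinic. The test is one-sided at 5 %.
- **Data analysis.** The model is named outright: "The primary analysis will employ multivariable linear regression to investigate differences in mean symptom scores (the primary outcome measure) between groups". It is applied to the month 3 and month 6 assessments. One adjustment is mentioned, and it is conditional: "adjusting for baseline outcome variables if imbalances are identified". Secondary outcomes are to be handled in a similar way. Clustering appears in this section only through the CONSORT guideline, "as well as its extensions to cluster and non-pharmacological interventions", which is cited for the data and the presentation of results.

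The section names no random effect, clinic-level summary, cluster-robust variance or municipality term.

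**The concern.** The sample size section treats patients of one clinic as correlated, while the model named for the primary outcome treats patients as independent. With two clinics per arm, any chance difference between clinics falls directly on the arm comparison. A regression that leaves clinic out judges that difference against patient-to-patient variation alone. Its standard error is then too small, its interval too narrow and its p-value too low. The same holds for SF-36 and OQ-45.2. The trial could report a training effect that is only variation between clinics, and the Discussion hopes the program can contribute to the national depression program.

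**Working it through.** **Inputs (Sample size and Group assignment sections).** Four clinics, two per arm; one-sided alpha 5 %; power 80 %; difference 20 points; ICC 0.03839; 368 analysed patients, so 368/4 = 92 per clinic.

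**1. The plan's own chain reproduces.**

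- Unclustered size, 58 % vs 38 %: [1.645·√(2·0.48·0.52) + 0.842·√(0.58·0.42 + 0.38·0.62)]² / 0.20² = 76.1, so 77 per group (154) against 76 (152) stated. With 55 % vs 35 % the result is exactly 76.
- Design effect: 1 + (m − 1)·ICC with m = 152/4 = 38 gives 1 + 37·0.03839 = 2.42.
- 152·2.42 = 367.8, so 368. Then 368/0.85 = 432.9, so 433 against 434 stated.

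The plan therefore does intend to allow for clustering when sizing the trial.

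**2. Standard error of a regression that omits clinic.** At 92 per clinic the design effect is 1 + 91·0.03839 = 4.49. The true standard error is √4.49 = 2.12 times the one reported.

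**3. False-positive rate.** One-sided: 1 − Φ(1.645/√DE). Two-sided: 2·[1 − Φ(1.96/√DE)]. At DE 4.49 these are 1 − Φ(0.776) = 21.9 % and 2·[1 − Φ(0.925)] = 35.5 %. In 100,000 simulated null trials (4 clinics × 92, normal outcome) the rates were 22.2 % and 35.9 %. Adding only a municipality term left them at 22.3 % and 36.2 %.

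| Assumed ICC | DE at 92 | One-sided 5 % | Two-sided 5 % |
|---|---|---|---|
| 0.005 | 1.455 | 8.6 % | 10.4 % |
| 0.01 | 1.91 | 11.7 % | 15.6 % |
| 0.02 | 2.82 | 16.4 % | 24.3 % |
| 0.03839 (plan) | 4.49 | 21.9 % | 35.5 % |
| 0.05 | 5.55 | 24.3 % | 40.5 % |

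**4. Effect of matching.** Suppose pairing by municipality removes a share f of the between-clinic variance. Then DE = 0.03839·(1 − f)·92 + (1 − 0.03839). For f = 0.5, 0.75 and 0.9 the one-sided rates are 16.0 %, 11.3 % and 7.6 %; the two-sided rates are 23.5 %, 14.9 % and 8.7 %.

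**5. Analyses that respect clinic, same null setting at the plan's ICC.**

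- Clinic-level t-test, 2 df: 5.0 % one-sided and two-sided.
- Matched-pair test, 1 df: 5.0 % and 5.1 %.
- ICC fixed at the planning value: 5 % if that value is right.
- Mixed model with municipality fixed and the clinic variance estimated: the estimate is zero in about 36 % of null trials, and the model then reverts to the naive regression. Overall error is about 8 % one-sided and 13 % two-sided.

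**6. Power of a valid analysis.** For 58 % vs 38 % the standardised difference is 0.20/√[(0.58·0.42 + 0.38·0.62)/2] = 0.409. Dividing by √(4·4.49/368) gives a non-centrality of 1.85. One-sided power at 5 % is about 58 % with a normal reference, 35 % on 2 df and 23 % on 1 df.

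**The case against.** The strongest reply is that the article never says clinic will be ignored. It names a regression, cites the CONSORT cluster extension, and shows in the sample size that its authors know about the ICC. A fuller analysis plan, not shown here, may add a clinic effect. A reader might infer that the investigators have decided to treat patients as independent; the document does not support that. What remains is that the article does fix the primary model and its covariates for a cluster trial, and that stated model has no place for clinic. A reporting guideline does not change the model. If another plan corrects it, this section still needs to agree.

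The size of the error is also open to challenge. The ICC comes from a small outside database, and the article does not say for which outcome. Pairing and baseline adjustment may both reduce the variation between clinics. This stands: the inflation is conditional, and at the low end it is under twofold for the one-sided test.

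A last reply is that the sample size already pays for clustering. It does not help here. Inflating the sample addresses power and does nothing for the standard error of a model without clinic. Larger clinics make that error worse.

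**Conclusion.** The point holds as a mismatch between the stated design and the stated primary model. Run as written, the regression understates the standard error by a factor of about 2.1 if the planning ICC applies to PHQ-9 scores and 92 patients per clinic are analysed. The relevant false-positive rate is about 22 %, because the plan's only stated test is one-sided; 36 % is the two-sided counterpart. It is tempting to conclude that the rate is certainly several times nominal. The documents do not support that: it falls to about 9 % at ICC 0.005 and to about 8 % if matching removes 90 % of the between-clinic variance. It stays above 5 % at every value examined. The text should be corrected before analysis.

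**What to change.** Replace the primary model in the Data analysis section with one that respects clinic and holds its level with four clusters. Choose one of these in advance:

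- **Clinic-level comparison** of baseline-adjusted PHQ-9 means, on 2 df, or on 1 df if paired by municipality.
- **Analysis with the clinic ICC fixed at 0.03839**, with a stated sensitivity range, for example the 0.005 to 0.05 tabulated above (that range is an assumption). This option holds 5 % only if the fixed value is not too low. If the true ICC were 0.05, the one-sided error would be 1 − Φ(1.645/√(5.55/4.49)) = 6.9 %.

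A mixed model with an estimated clinic variance should be supportive only, for the reason in step 5. A fixed clinic effect is not an option, because clinic determines arm. Use the same approach for SF-36 and OQ-45.2.

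The cost is more than wording. Intervals become much wider, and power for the planned 20-point difference drops to the figures in step 6, well below 80 %. The Sample size section says that finances rule out more clinics. The power statement should therefore be restated, and conclusions should be worded around the interval and not around significance.

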Since 2001, Chile has had a program for the detection, diagnosis, and treatment of depression in primary care clinics. It recommends algorithms for diagnostic evaluation, delivery of psychosocial interventions and medications, consultations with specialists, follow-up visits, and criteria for referral to secondary care. All persons with depression have to be treated in primary care unless they have psychosis, bipolar disorder, high suicidal risk, or a lack of response to two courses of treatment with two different antidepressants at therapeutic doses, plus psychosocial intervention [10].

In 2006, depression was incorporated into the national health reform, thus ensuring universal access to treatment for depressed individuals 15 and older [11], the majority of whom are treated by primary care teams [12]. Since 2009, the Ministry of Health has published two Clinical Guidelines for depression treatment, but no training program has yet been recommended [10, 13].

An evaluation of the depression program carried out at seven primary care clinics in two regions of Chile demonstrated that diagnoses of the severity of illnesses were inaccurate, that severity of depressive episodes was underestimated, that treatments were not indicated according to the severity of the illness or according to guidelines, that adherence to treatment was insufficient − higher for pharmacological treatment and lower for individual psychotherapy and group psychoeducation − and that patient dropout from the program was around 60 % [14, 15].

International evidence indicates that, despite the high prevalence of depression and availability of effective treatments, the diagnosis and treatment of depression by general practitioners do not follow clinical guidelines and that these guidelines do not always include training [16, 17].

Training can improve the detection, diagnosis, and treatment and could lead to better patient outcomes, although studies have shown that training alone does not result in improved outcomes [18, 19].

There is abundant literature on the effectiveness of collaborative care on depression [20]. Systematic literature reviews of strategies employed to improve mental health patient outcomes reported that the most effective interventions incorporate clinician education, nurse case management, a greater integration between primary and secondary care [21], and quality measures to improve results [22].

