### Intervention arm

The intervention arm includes a 16-h training program for primary care teams (physicians, psychologists, social workers, nurses, midwives, and occupational therapists) to ensure compliance with the Clinical Guidelines for the Treatment of Depression, issued by the Chilean Ministry of Health [10]. The workshop will include a seminar on the detection, diagnosis, and treatment of depression; discussion of clinical cases; and role-playing to enhance clinical skills and to apply problem-solving techniques. Finally, trained primary care teams will undergo an Objective Structured Clinical Examination (OSCE) for evaluation.

After the training, a focus group between primary health care teams and study researchers will be held in order to address barriers to the implementation of clinical guidelines. In order to develop a comprehensive supervision program, trained administrative staff will contact patients from a call center to support treatment adherence, and a psychiatrists will supervise the primary care team, using a web-based platform.

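### The primary linear regression, read as written, ignores the 3-month PHQ-9 of patients lost by 6 months, so arm-related dropout can bias the 6-month difference

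*Protocol article*

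**What the plan says.** The Data analysis section of the protocol article makes four relevant statements.

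- Model: "The primary analysis will employ multivariable linear regression to investigate differences in mean symptom scores".
- Timing and covariates: the comparison is "between groups at 3 and 6 months after randomization, adjusting for baseline outcome variables if imbalances are identified".
- Population: "with the primary comparative analysis being conducted on an intention-to-treat basis".
- Missing data: "Sensitivity analysis based on different assumptions will be conducted to investigate the potential effects of missing data".

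The Sample size section sets the expected loss: "Considering a retention rate of approximately 85 %, 434 depressed cases will be required for the study". Under Intervention arm, "trained administrative staff will contact patients from a call center to support treatment adherence"; the Control arm section describes no such contact. Under Data collection, every participant is assessed at baseline, 3 months and 6 months.

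**The concern.** An ordinary linear regression cannot use a record whose outcome is missing. A patient seen at baseline and 3 months but lost by 6 months adds nothing to the 6-month difference, although the 3-month PHQ-9 says a good deal about where that patient was heading. The text names no repeated-measures model and no imputation for the primary result.

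This matters here for two reasons. The intervention is designed to change adherence and contact, and the trial hypothesises better adherence in that arm, so retention that differs by arm and tracks response is plausible. In addition, baseline PHQ-9 enters the model only if an imbalance is noticed, so protection against dropout driven by baseline severity is not guaranteed either. At stake is a 6-month treatment difference shifted up or down by dropout, when data that could largely correct the shift have been collected.

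**Working it through.** **The plan's own figures.** 368 / 0.85 = 432.9, against 434 stated. 434 × 0.85 = 368.9, against 368 needed. The expected loss is 434 − 368 = 66 patients (15.2 %).

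**What the documents do not give.** There is no PHQ-9 SD, no correlation between visits and no dropout by arm. Everything below rests on assumptions.

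**Assumed inputs.** SD 5.5; true effect 0; correlation of the 6-month score about 0.5 with baseline and about 0.6 with the 3-month score. Where dropout depends on severity, the log-odds of missing the 6-month visit change by 0.7 per SD. All patients have a 3-month score.

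**Definition.** Bias = (mean 6-month score among those observed, intervention − control) − true difference. If higher scores are lost more often from control, control looks better than it is and the bias is positive, against the intervention. Three estimators were compared by large-sample simulation (2 million records): available-case unadjusted, available-case adjusted for baseline, and a missing-at-random method predicting the missing 6-month score within arm from baseline and the 3-month score.

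| Dropout depends on | Missing, control / intervention | Unadjusted | Baseline-adjusted | Using baseline and 3-month score |
|---|---|---|---|---|
| Baseline, same slope | 20 % / 10 % | 0.17 | 0.0 | 0.0 |
| Baseline, opposite slopes | 15 % / 15 % | 0.55 | 0.0 | 0.0 |
| 3-month score, same slope | 20 % / 10 % | 0.21 | 0.12 | 0.0 |
| 3-month score, control only | 20 % / 10 % | 0.45 | 0.26 | 0.0 |
| 3-month score, opposite slopes | 15 % / 15 % | 0.65 | 0.38 | 0.0 |

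**Analytic check of the last two unadjusted figures.** Unadjusted bias = correlation × SD × (difference between arms in the mean standardised 3-month score of those retained). Numerical integration gives a retained mean of −0.130 at 20 % missing and slope 0.7, and ∓0.0986 at 15 % missing and slope ±0.7. With a 3-to-6-month correlation of 0.605:

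- control only: 0.605 × 5.5 × 0.130 = 0.43 (simulated 0.45);
- opposite slopes: 0.605 × 5.5 × (0.0986 + 0.0986) = 0.66 (simulated 0.65).

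**A second set.** 217 per arm, SD 6, true effect −2, 20 % control dropout rising with the 3-month score, 12 % random dropout in the intervention arm, 2000 trials. For slopes of 0.4 to 1.0 the bias was +0.29 to +0.62 unadjusted and +0.17 to +0.36 baseline-adjusted. It was within 0.01 of zero for an estimator using the 3-month score.

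**Equal dropout.** With 15 % lost in each arm, the same slope of 0.7 on the 3-month score and SD 6, the bias was 0.005 unadjusted and 0.004 adjusted, in effect none.

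**Scaling.** Bias is proportional to the SD. At SD 6 the largest table entries become 0.65 × 6 / 5.5 = 0.71 and 0.38 × 6 / 5.5 = 0.41.

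**Against the sampling error.** With 184 analysed per arm, SD 6 and the article's design effect of 2.42 taken at face value, SE = 6 × √(2/184) × √2.42 = 0.626 × 1.556 = 0.97 points. A bias of 0.38 is 0.38 / 0.97 = 0.4 SE; one of 0.65 is about 0.7 SE.

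**The case against.** The strongest reply is that this is a condensed article. The handling of missing outcomes is commonly left to a full protocol or analysis plan that is not shown, and linear regression is compatible with multiple imputation using the 3-month score. That is right as far as silence goes, and silence is not the point. The article fixes the primary model, makes baseline adjustment conditional and places missing data under sensitivity analysis only. The point is that this stated choice is weaker than a readily available alternative.

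Several stronger readings are tempting, and the documents do not support them.

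- *Each visit has its own regression and incomplete patients are removed.* The text says neither; this is the ordinary reading of the named method. A single ordinary regression pooling both visits would still not use a 3-month score to inform a missing 6-month one.
- *The intention-to-treat statement is contradicted.* It is not. That principle governs who is compared and in which arm, and does not dictate a missing-data method. The model proposed below also leaves out patients with no follow-up score.
- *The result is invalid whenever dropout depends on the 3-month score, or differs by arm and severity.* Both are too broad. Equal rates and slopes gave no material bias. Dropout driven by arm and baseline severity gave none once baseline was in the model.
- *Missing data are overlooked.* The article commits to sensitivity analyses. These leave the primary result as it is, but their content is unseen and cannot be judged.
- *Loss could approach the Background figure, where* "patient dropout from the program was around 60" *%.* That is dropout from the treatment programme, not loss to study follow-up. An extreme case of 60 % against 15 % gives 1.25 points unadjusted and 0.74 adjusted, but nothing in the plan predicts it.

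It also stands that the gain in precision is small (an SD of the estimate of 0.534 against 0.543 in one run), and that the bias is below one standard error in every scenario at the planned loss.

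**Conclusion.** The concern holds in a limited form. As written, the primary 6-month comparison makes no use of the 3-month scores of patients lost later, and it may not adjust for baseline. Bias follows if the rate or mechanism of dropout differs between arms and depends on post-baseline severity, or on baseline severity when baseline is left out. At about the planned loss, its size was roughly 0 to 0.65 PHQ-9 points unadjusted and 0 to 0.4 baseline-adjusted (0.71 and 0.41 if the worst case is rescaled to SD 6). It could run in either direction.

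These figures rest on assumed SDs, correlations and dropout patterns; none is in the documents. The near-zero bias of the alternative assumes that data are missing at random given baseline and the 3-month score, and that patients lost by 6 months had been seen at 3 months. The change is worth making because it is cheap and improves the method; the stated plan is not shown to be invalid.

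**What to change.** Make the primary analysis one repeated-measures linear model of the 3- and 6-month PHQ-9. Include arm, visit, arm-by-visit, baseline PHQ-9 in all cases, and municipality as a fixed effect, and allow for the correlation between a patient's two scores. Use every participant with at least one follow-up score, and read both arm differences from this model. Keep the planned sensitivity analyses, directed at data missing not at random and at patients with no follow-up score.

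The cost is a rewritten analysis paragraph and slightly more analysis work; the model can be fitted in SPSS. The limits are the missing-at-random assumption and the 3-month comparison: when dropout is monotone, a patient lost before 3 months has no later score, so that comparison gains nothing. How clinic clustering should be handled with only four clinics is a separate question that this change does not settle.

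### Whether baseline PHQ-9 enters the primary model is decided after looking at the data, under a criterion for imbalance that is not defined

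*Protocol article*

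**What the plan says.** The Data analysis section of the protocol article sets out two steps. The first is a look at the baseline data: "Initially, we will conduct descriptive analysis to assess the balance between the two groups". The second is the model: "The primary analysis will employ multivariable linear regression to investigate differences in mean symptom scores (the primary outcome measure) between groups". It is fitted for both follow-up assessments, and its covariates carry a condition: "adjusting for baseline outcome variables if imbalances are identified". The same approach is to be used for the secondary outcomes. The section does not say what counts as an imbalance or who decides.

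The Data collection section states: "All participants will be assessed at baseline and at 3 and 6 months after recruitment". The baseline score is therefore planned for every participant, whatever the balance check shows.

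**The concern.** The plan makes the content of the primary model depend on the result of the balance check. This is a rule that the article states, not a detail left to a fuller document. A separate analysis plan could define a threshold for imbalance, but the covariate set would still be chosen from the data.

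Two things are at stake. First, two analysts who both follow the plan could fit different primary models and report different estimates. Only four clinics are randomised, two per arm, so a visible baseline difference is quite possible and the reading of the rule matters. Second, when no imbalance is declared, whatever baseline gap exists stays in the treatment estimate, and the precision that the baseline score offers is given up.

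**Working it through.** **Inputs from the protocol article (Sample size, Group assignment).** ICC 0.03839; four clinics, two per arm; 152 patients before clustering; design effect 2.42; 368 after it; 109 recruited per clinic.

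**The plan's own figures.** With 152/4 = 38 patients per clinic, 1 + 37 × 0.03839 = 2.42. Then 152 × 2.42 = 367.8, or 368, which is 368/4 = 92 analysed per clinic. None of these figures uses baseline adjustment, so the sample size does not bear on the point either way.

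**Assumptions, because the article gives no figure.** The correlation r between baseline and follow-up PHQ-9 is 0.4 to 0.6, with similar standard deviations at both times. The stated ICC applies to PHQ-9 at baseline and at follow-up.

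**1. Bias left in when a gap is not declared an imbalance.** With similar standard deviations, the slope of follow-up on baseline is about r. A 1-point gap left unadjusted therefore moves the follow-up difference by about 0.4 to 0.6 points.

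**2. Precision at patient level.** Adjustment removes r² of the patient-level residual variance: 0.4² = 16%, 0.6² = 36%.

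**3. Precision of the treatment effect.** In units of the total variance, a clinic mean has variance 0.03839 + 0.96161/92 = 0.03839 + 0.01045 = 0.04884. With two clinics per arm, the difference between arms has variance 2 × 0.04884/2 = 0.04884.
- The patient-level share is 0.01045/0.04884 = 21%.
- The reduction from adjustment is 0.16 × 0.214 = 3.4% to 0.36 × 0.214 = 7.7%, so about 3 to 8%.
- The unadjusted standard error is larger by 1/√0.966 − 1 = 1.8% to 1/√0.923 − 1 = 4.1%.
- If baseline also explains differences between clinics, the reduction is larger. It reaches 16 to 36% if baseline explains the same share r² at both levels.
- Between-clinic variance shared by the two clinics of a municipality cancels from the arm difference, which also raises the patient-level share. If half is shared, the share is 0.01045/(0.01920 + 0.01045) = 35% and the reduction is about 6 to 13%.

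**4. How often two readings of the rule disagree.** With 109 per clinic, the chance baseline gap between arms has standard deviation √(0.03839 + 0.96161/109) = 0.217 patient-level SDs. A plain t-test at p < 0.05 calls an imbalance beyond 1.96 × √(2/218) = 0.188. A standardised-difference rule might use 0.1.

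| Share of between-clinic variance due to municipality | SD of gap | Adjusts under p < 0.05 | Adjusts under difference > 0.1 |
|---|---|---|---|
| 0 | 0.22 | 39% | 65% |
| 50% | 0.17 | 26% | 55% |
| 90% | 0.11 | 10% | 37% |

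In roughly 26 to 29% of trials, the two readings lead to different primary models.

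**5. Type I error of the conditional rule.** This was simulated with 184 per arm, 5000 runs, no clustering, and imbalance taken as baseline p < 0.05. At r = 0.3, 0.5 and 0.7, the one-sided error was 5.0%, 4.6% and 3.9% against a nominal 5%.

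**The case against.** **If an imbalance is likely, the rule will often trigger adjustment.** This stands in part. The shift in step 1 arises only when a gap exists and is not declared. The complaint is that the decision depends on the data and has no criterion, not that adjustment will usually be absent.

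**The gain in precision is modest here.** This stands. A reader might take the 16 to 36% as the gain in the treatment effect, but that holds only if baseline explains between-clinic variance equally well. At the stated ICC, most of the variance of a clinic mean lies between clinics. A simulation at a true effect of 0.2 SD gave power of 62% for the conditional rule against 72% for constant adjustment at r = 0.5. It ignored clustering, so it overstates the gain to the extent that clinic-level variance remains.

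**The conditional rule does not produce false positives.** This stands as far as it was tested. A reader might infer inflated type I error, but the simulation in step 5 shows none. It also ignored clustering.

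**The matched design.** Each municipality contributes two clinics, "one from the intervention arm and one from the control arm, in each selected municipality". A reader might infer that the pairs are left out of the model and that a municipality fixed effect is needed. The article does not support this:
- It calls the model multivariable, lists no full covariate set, excludes nothing, and cites CONSORT "as well as its extensions to cluster and non-pharmacological interventions". A condensed article commonly leaves the covariate list to a fuller document.
- One clinic per arm in each municipality already balances that factor. With equal numbers per clinic, the point estimate is the same with or without the term.
- In simulated patient-level regression at a true effect of 0.4 SD, rejection hardly moved: 84.9% against 85.0%, 90.8% against 91.0% and 97.3% against 97.6% when municipality carried 0, 50% and 90% of between-clinic variance.
- In a clinic-level analysis the term takes one of two residual degrees of freedom, and the one-sided 5% critical t rises from 2.92 to 6.31. Power went from 33% to 21%, from 35% to 29%, and from 38% to 40% for the same three shares.

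**Conclusion.** The point holds for the conditional adjustment and should be corrected. The article lets the observed data decide, under an undefined criterion, whether baseline PHQ-9 is in the primary model, although the score is planned for everyone.

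The size is moderate. An undeclared gap carries over at about 0.4 to 0.6 PHQ-9 points per baseline point. The loss of precision is about 3 to 8% of the variance of the treatment effect, and more if baseline also explains differences between clinics or if the two clinics of a municipality share part of the between-clinic variance. These figures rest on the assumed correlation of 0.4 to 0.6, on similar standard deviations, and on the stated ICC applying to PHQ-9. The ambiguity in the rule depends on none of these assumptions.

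The point does not extend to type I error or to a required municipality term.

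**What to change.** In the Data analysis section, delete the condition in "adjusting for baseline outcome variables if imbalances are identified". State that the primary model always includes baseline PHQ-9, and that each secondary analysis includes the baseline score of its own scale (SF-36, OQ 45.2), whatever the baseline table shows. Report the unadjusted result as supportive. The descriptive comparison of the groups can stay, as description only.

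The cost is one sentence. No new data are needed, because the baseline assessment is already planned for all participants, and nothing in the conduct of the trial changes.
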